**Study procedure:**

*Lesion collection*

Lesions used in the present study will be prospectively acquired in the clinical study named CHANGE. Patients enrolled will undergo a standard white-light colonoscopy with the support of the latest version of the CE-marked GIG CADx device (version 3.0.0). Colonoscopy will be performed according to the standard practice. The primary endpoint of CHANGE study is to measure the Negative Predictive Value (NPV) of GI Genius CADx optical diagnosis on diminutive ( $\leq 5$  mm) rectosigmoid polyps. CHANGE study estimated enrolment is of 156 participants, corresponding to a total of about 500-800 lesions. First valid 504 lesions resected in the CHANGE study will be included in the Standalone CADx study.

*Electronic data recording*

All endoscopy procedures in the CHANGE study will be recorded lossless (without image degradation or compression) and without any of the GI Genius markings from beginning to the end of the procedure. In other words, the video of the recorded procedures will bear no trace of the AI used. All clinical data of the participants and of the retrieved lesion will be recorded in an electronic CRF using openclinica ([www.openclinica.com](http://www.openclinica.com)).

*Batch subdivision*

For the Standalone CADx study, the following process will be used for video preparation. Every 84 consecutive lesions will be considered as an independent batch. Batches will be numbered in progressive order: batch01, batch02, etc. As soon as a batch is completed all video recordings in the batch will be prepared for lesion review. With this strategy, the review of the lesions via the website needed for the present study will be run in parallel to the acquisition of the patient in the CHANGE study.

*Videoclip check and annotation*

All video procedures from a given batch will be carefully examined by scientific annotator experts in the task of video preparation for artificial intelligence elaboration. In particular, the timing and the localization of each lesion in each patient of the batch will be carefully annotated and confronted with data of the lesion in the eCRF for the same patient, to avoid any possibility of erroneous correspondence between lesion in the video and following histology outcome. Lesions for which no recording is available will be excluded from Standalone CADx study.

For each lesion, a short video clip will be prepared, starting a few seconds before the first lesion appearance and ending with lesion surgical resection. If multiple lesions are present in the same video section, a separate clip will be generated for each individual lesion. During the first ten seconds of the videoclip, a green box will be manually drawn (overlaid) around the target lesion. There will be no other graphical marks except for this green box indicating the lesion position. The purpose of this marking is to avoid to the endoscopist reviewing the clip any ambiguity in identifying which is the region of interest about which it is asked to express a prediction of the histology. To be noted that the markings is not generated by AI, and its only purpose is to clearly identify lesion to be assessed. Consequently, in Standalone CADx study there is no interaction between AI-generated content and humans.

*Optical characterization of lesions by endoscopists reviewers*

After the procedure has been carried out and data relative to colonoscopy has been properly recorded in eCRF, before the availability of the histology results, without the presence of the patient and the endoscopist who has performed the procedure, the video recording will be reviewed by a team of endoscopists reviewers to get their optical biopsies and confidence about polyp adenomatous or non-adenomatous histology.

*Randomization*

Overall, we will use in Standalone CADx study 6 batches with 84 lesions each, for a total of 504 lesions. Possible further lesions that will be available from the CHANGE study are not going to be used in the present experiment. For each batch, 20 pre-randomization lists will be prepared for the order of presentation of lesions. Each endoscopist reviewer will be preassigned a pre-randomization ID, and lesions in each batch will be presented to the reviewer with the order corresponding to the pre-randomization ID.

*Online survey*

Data will be collected by means of an online survey. Each participant will be provided with a unique username. The video interface (see figure above) will allow the user to fully control what to play, allowing the endoscopist to skip, view again, pause, etc. We will record the viewing time for each frame.

A. Please classify the lesion in the video in one of the following categories:

1. Adenoma
2. Hyperplastic

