| 
Objective:
 
To prospectively evaluate if GI Genius CADx accuracy in the automated OC of colorectal polyps in white light is non-inferior to the accuracy of expert endoscopists performing OC (supported by virtual chromoendoscopy), having histopathology as a reference standard.
 
Furthermore, to evaluate if GI Genius CADx accuracy in the automated OC of colorectal polyps in white light is superior to the accuracy of non-expert endoscopists performing OC (supported by virtual chromoendoscopy), having histopathology as a reference standard.
 
Furthermore, to evaluate if GI Genius CADx accuracy in the automated OC of colorectal polyps in white light is non-inferior to GI Genius CADx accuracy in virtual chromoendoscopy, having histopathology as a reference standard.
                                                                                                                                                                                                                                                                                                                                                                                                                                                                                                                                                                                                                                                                                                                                                                                                                                                                                                                                                                                                                                                                                                                                            |

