| 
Endoscopist reviewers invitation:
 
After Standalone CADx protocol registration, we will send invitations to expert and non-expert endoscopist reviewers who will be asked to perform optical characterization of video recordings of lesions collected in CHANGE study.
 
Experts are endoscopists having more than 5 years of colonoscopy experience, a proven track of scientific publications on optical characterization or a similar subject, and experience in optical biopsy with virtual chromoendoscopy. An endoscopist is considered “non-expert” if s/he has performed less than 500 colonoscopies.
 
Our minimum target number of reviewers completing the whole set of stimuli is 16: 8 experts, and 8 non-experts. To reach the target in each subgroup we will send 20 invitations in the first wave, considering a 20% dropout. If less than 8 + 8 reviewers agreed to participate in the study after two weeks, a second wave of 10 invitations will be sent (weighted for the proportion of missing reviewers in the two main classes). The same criterion and waiting time will be applied to the possible successive invitation waves. Once the targeted participant pool has been reached, we will stop invitations.
 
After the data acquisition has started, we will monitor for potential dropouts. Whenever the total active reviewers fall below the minimum targeted values (8+8) we will resume invitation with a ratio of 2:1, i.e., two invitations for each participant missing to the target. Thus, if we find ourselves with 7 non-expert participants because of dropouts, we will invite another 2.
 
The data collection for Standalone CADx study will be closed when at least 8 non-expert and 8 expert endoscopists will have completed all required evaluations.
 
All data will be used in the analyses, even if data collection produced slightly more data than the minimum target.
 |

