## **Study endpoints:**

### **Primary endpoint:**

1. GI Genius CADx accuracy in white light is non-inferior to the accuracy of expert endoscopists, having histopathology as a reference standard.

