## **Analysis plan:**

1. Test for non-inferiority of GI Genius CADx accuracy in white light against accuracy of expert endoscopists supported by virtual chromoendoscopy, having histopathology as a reference standard, with a margin of 10%.
2. Test for superiority of GI Genius CADx accuracy in white light against accuracy of non-expert endoscopists supported by virtual chromoendoscopy, having histopathology as a reference standard.
3. Test for non-inferiority of GI Genius CADx accuracy in white light against GI Genius CADx accuracy in virtual chromoendoscopy, having histopathology as a reference standard.
4. Report descriptive analysis of Sensitivity, Specificity, Accuracy, of GI Genius CADx optical characterization for different subdivision of lesion according to size, anatomical location, endoscope, age, sex, reason for colonoscopy.

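### Expert reads described as chromoendoscopy-supported can be given without viewing any chromoendoscopy, which could tilt the non-inferiority test toward CADx

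*Protocol*

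**What the plan says.** The Objective of the Standalone CADx synopsis asks whether the white-light accuracy of CADx "is non-inferior to the accuracy of expert endoscopists performing OC (supported by virtual chromoendoscopy), having histopathology as a reference standard". Analysis plan item 1 tests CADx "against accuracy of expert endoscopists supported by virtual chromoendoscopy", with a margin of 10%, and item 2 gives the non-experts the same support. The Primary endpoint is shorter and does not mention chromoendoscopy: "GI Genius CADx accuracy in white light is non-inferior to the accuracy of expert endoscopists, having histopathology as a reference standard".

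The expert reads are produced as follows:

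- **Clip.** Each clip runs from just before the lesion appears until its resection (Study procedure). In the CHANGE procedure (CHANGE synopsis item 11; CHANGE protocol section 7, Colonoscopy visit) blue light is switched on only after the white-light assessment. Blue-light footage is therefore expected in the clip, but after the white-light part. A green box marks the target lesion during the first ten seconds.
- **Player.** Playback is under the full control of the reviewer, "allowing the endoscopist to skip, view again, pause, etc. We will record the viewing time for each frame".
- **Answer.** Question A asks for a lesion category, and a recorded answer is final. No instruction mentions blue light.
- **Derived variable.** Under Measurement variables, the reviewer prediction depends only on the answer to question A. The CADx white-light and blue-light predictions, by contrast, are each defined by an exact subset of frames.

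**The concern.** The protocol fixes the light mode for one side of the primary comparison and leaves it open for the other. CADx in white light is built from white-light frames and nothing else. The expert side is described as chromoendoscopy-supported, yet no step in the reading procedure secures that. A reviewer can find the lesion from the green box, decide on white light and store a final answer before any blue light appears.

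In a non-inferiority test, whatever weakens the comparator helps the claim. If a material share of expert reads were white-light reads and were less accurate for that reason, the trial could report that CADx in white light holds up against experts using chromoendoscopy when part of the comparison was with experts not using it. The exploratory superiority test against non-experts uses the same survey and would lean the same way.

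**Working it through.** **The plan's own figure.** The Sample size section gives CADx 85%, experts 87%, one-sided alpha 0.025 and 80% power; the margin of 10% is in the Analysis plan. With one independent read per lesion on each side:

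- discordance = 0.87 × 0.15 + 0.85 × 0.13 = 0.241
- paired n = (0.241 − 0.02²) × (1.960 + 0.842)² / 0.08² = 295.1, so 296 lesions (or 296 per group, 592 in all, if treated as two independent groups)

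The stated 480 is not reproduced on either basis, although 480 × 1.05 = 504 is. That is a separate matter, and nothing below rests on 480.

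**Size of the tilt.** Let s be the share of expert reads made without blue light and d the accuracy lost on those reads. Apparent expert accuracy is then 87% − s × d, and the effective margin against experts who did view blue light is 10% + s × d. Neither s nor d is in the documents; the ranges are assumptions.

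| s | d = 2 points | d = 5 points | d = 10 points |
|---|---|---|---|
| 10% | 0.2 | 0.5 | 1.0 |
| 25% | 0.5 | 1.25 | 2.5 |
| 50% | 1.0 | 2.5 | 5.0 |

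Apparent expert accuracy runs from 86.8% (87 − 0.2) down to 82.0% (87 − 5), and the effective margin from 10.2% to 15.0%. At s = 25% and d = 10 points, the planned difference of 85 − 87 = −2 points would appear as 85 − 84.5 = +0.5. If d = 0, nothing changes.

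**Effect on the error rate (illustrative).** Suppose CADx is truly at the margin against experts who view blue light: 77% against 87%. Let b = s × d, p = 0.87 − b and q = 0.77, with 504 lesions and one independent read per lesion:

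- V = p(1 − q) + q(1 − p) − (p − q)²
- false non-inferiority rate = Φ( b / √(V/504) − 1.960 )

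For b = 0.01: V = 0.1978 + 0.1078 − 0.0081 = 0.2975, the standard error is 0.0243, and Φ(0.412 − 1.960) = 6.1%.

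| Tilt b (points) | False non-inferiority |
|---|---|
| 0 | 2.5% |
| 0.5 | 4.0% |
| 1 | 6.1% |
| 2 | 12.6% |
| 2.5 | 17.1% |
| 5 | about 50% |

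These rates ignore multiple readers per lesion and clustering of lesions within patients. They show direction and order of magnitude only.

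**The case against.** The strongest reply is that support means availability. The footage is in the clip, and the experts are chosen for experience with chromoendoscopy and publications in the field. An expert who skips it may already be certain, and then no accuracy is lost. Replay and pausing come with the same controls and may raise expert accuracy. Clips are short and released in batches of 84, and a doubtful reader can watch again or answer that the lesion is uncertain. The per-frame log makes the matter measurable, and a statistical analysis plan not shown here may use it.

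Much of this stands. Three stronger readings are tempting, and the documents do not support them:

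- **That expert accuracy will be lowered.** The documents do not show that reviewers will skip blue light, how often, or at what cost.
- **That the protocol commits to counting every such read.** The sentence "All data will be used in the analyses, even if data collection produced slightly more data than the minimum target" concerns reviewers beyond the target number, not the validity of a read. The firmer basis is that the reviewer prediction is defined by the answer alone.
- **That CADx sees the whole clip while experts may not.** In the primary test CADx is itself confined to white-light frames.

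What the reply does not remove is the ambiguity. Support available and support used are different comparators, and the protocol does not choose between them. An analysis plan can sort reads by the log afterwards, but it cannot make a reviewer see the footage before the answer is locked.

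**Conclusion.** The point holds as a gap in the design, not as a demonstrated bias. The reading procedure does not secure the comparator named in the objective and primary test. If reads without blue light are less accurate, the error favours CADx. For the assumed ranges the tilt is 0.2 to 5 points, and a 1-point tilt would raise the illustrative false non-inferiority rate from 2.5% to about 6%. The tilt is zero if experts skip only when blue light would not change their answer. The change is worth making because it is cheap and has to be made before reads are collected. Confidence is medium, since both the share of such reads and their accuracy cost are unknown.

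**What to change.** 1. Open question A only after the clip's blue-light segment, where there is one, has been played at least once. Leave skipping and replay otherwise free. Support available and support viewed then coincide.
2. Keep all reads in the primary comparison. Limiting it to reads with blue light viewed would select on reader behaviour: if experts skip blue light on obvious lesions, their easiest and most accurate reads would be lost, which could itself favour CADx.
3. Prespecify a sensitivity analysis from the frame-level viewing log, limited to reads with blue light viewed and with CADx accuracy computed on the same reader-lesion pairs. This also covers any reads stored before the player is changed.

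The cost is a setting in the survey player, a sentence or two in the plan, and slightly longer reading time per clip. The log is already being collected.

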3. SSL
4. Carcinoma
5. Uncertain

B. Your level of confidence relative to question A:

1. Very high confidence
2. High confidence
3. Low confidence
4. Very low confidence

[figure not shown]

The endoscopist reviewers need to answer the following questions:

A. Please classify the lesion in the video in one of the following categories:

1. Adenoma
2. Hyperplastic
3. SSL
4. Carcinoma
5. Uncertain

B. Your level of confidence relative to question A:

1. Very high confidence
2. High confidence
3. Low confidence
4. Very low confidence

Question B will be offered only in case the participant does not choose “Uncertain” in question A.

All response times will be logged. It will not be possible to change the answer to one question once it has been recorded.

According to the study procedure described above there is no interaction between AI-generated content and humans. Consequently, all endoscopist reviewer answers regarding the lesion optical characterization are decided solely according to their clinical experience, without any AI output.

The data collection for Standalone CADx study via the online survey will be closed when at least 8 non-expert and 8 expert endoscopists will have completed all required evaluations.

### Measurement variables:

**GI Genius CADx prediction:** the diagnosis about a given lesion provided by GI Genius. It takes the following values: “adenoma”, “non-adenoma”, and “undetermined”. The output of GI Genius CADx for a given lesion is a time series with a unique value for each image frame, starting with the first GI Genius CADE detection of the lesion and terminating at the last image frame of the video clip, when the lesion is resected. Of all time frames when the lesion is visible, only those where GI Genius CADx has expressed one of the possible three labels are considered: “adenoma” / “non-adenoma” / “no-prediction”. The GI Genius CADx prediction will be considered “adenoma” if the number of frames where GI Genius CADx outputs the label “adenoma” is greater than or equal to the number of frames where GI Genius CADx outputs “non-adenoma”. The GI Genius CADx prediction will be considered “non-adenoma” if the number of frames where GI Genius CADx outputs the label “non-adenoma” is greater than the number of frames where GI Genius CADx outputs “adenoma”. If GI Genius CADx fails to output either the label “adenoma” or “non-adenoma” for the entire clip of a given lesion, the GI Genius CADx prediction will be considered “undetermined”.

**GI Genius CADx prediction in white light:** the GI Genius CADx prediction according to the method described above, considering only the frames in white light (the subset of the lesion frame timeseries in white light).

**GI Genius CADx prediction in blu light:** the GI Genius CADx prediction according to the method described above, considering only the frames in blu light (the subset of the lesion frame timeseries when virtual chromoendoscopy is activated).

**GI Genius CADx confidence:** the degree of certainty about the response (prediction) given by GI Genius CADx. It takes the following values: “high confidence”, “low confidence”, and “undetermined”. GI Genius CADx confidence will be considered “undetermined” if the GI Genius CADx prediction is “undetermined”. GI Genius CADx confidence will be considered “low confidence” if the number of frames where GI Genius CADx outputs the label “no-prediction” is greater than or equal to the sum of the number of frames where GI Genius CADx outputs “adenoma” and the number of frames where GI Genius CADx outputs “non-adenoma”. GI Genius CADx confidence will be considered “high confidence” if the number of frames where GI Genius CADx outputs the label

“no-prediction” is smaller than the sum of the number of frames where GI Genius CADx outputs “adenoma” and the number of frames where GI Genius CADx outputs “non-adenoma”.

*Endoscopist reviewer prediction:* the diagnosis about a given lesion provided by a reviewer. It takes the following values: “adenoma”, “non-adenoma”, and “undetermined”. The endoscopist reviewer prediction for a specific lesion will be considered “adenoma” if the corresponding answer to the question A of the online survey is “1. Adenoma” or “4. Carcinoma”. The endoscopist reviewer prediction for a specific lesion will be considered “non-adenoma” if the corresponding answer to the question A of the online survey is “2. Hyperplastic” or “3. SSL”. The endoscopist reviewer prediction for a specific lesion will be considered “undetermined” if the corresponding answer to the question 1 of the online survey is “5. Uncertain”.

*Endoscopist reviewer confidence:* the degree of certainty about the response (prediction) provided about a given lesion. It takes the following values: “high confidence”, “low confidence”, and “undetermined”. The endoscopist reviewer confidence for a specific lesion will be considered “high confidence” if the corresponding answer to the question B of the online survey is “1. Very high confidence” or “2. High confidence”. The endoscopist reviewer confidence for a specific lesion will be considered “low confidence” if the corresponding answer to the question B of the online survey is “3. Low confidence” or “4. Very low confidence”. The endoscopist reviewer confidence for a specific lesion will be considered “undetermined” if the corresponding answer to the question A of the online survey is “5. Uncertain”.

*Histology ground truth:* the histopathological evaluation provided about a given lesion. It takes the following values: “adenoma”, and “non-adenoma”. The histopathological evaluation will be based on the revised Vienna classification of gastrointestinal epithelial neoplasia. Lesions corresponding to Vienna category 1 (negative for neoplasia) or 2 (indefinite for neoplasia) will be considered “non-adenoma”. Lesions corresponding to Vienna category 3 (mucosal low-grade neoplasia), 4 (mucosal high-grade neoplasia) or 5 (submucosal invasion of neoplasia), will be considered “adenoma”.

## **Study endpoints:**

### **Primary endpoint:**

1. GI Genius CADx accuracy in white light is non-inferior to the accuracy of expert endoscopists, having histopathology as a reference standard.

### **Exploratory endpoints:**

1. GI Genius CADx accuracy in white light is superior to the accuracy of non-expert endoscopists, having histopathology as a reference standard.
2. GI Genius CADx accuracy in white light is non-inferior to GI Genius CADx accuracy in blu light (virtual chromoendoscopy), having histopathology as a reference standard.

